#### Secondary outcome measures

A VAS will be used to evaluate severity of pain during sports and daily activities for the past 7 days. The VAS is a 100 mm horizontal line with two anchors, where zero represents ‘no pain at all’, and 100 represents ‘the most severe pain’. It has been shown to be a valid and reliable method for evaluating pain levels. [37].

To determine whether participants feel that they have benefited from the intervention, global perceived effect (GPE) will be measured with the GPE scale. [38] This is a 7-point ordinal scale, ranging from “completely recovered” to “worse than ever”.

The effect of the exercise programs on QOL will be assessed with the 12-item Short Form Health Survey (SF-12) [39] and the Euroqol instrument (EQ-5D) [40] during baseline and follow-up measurements.

To assess functional performance of the muscle-tendon unit, two different tests with acceptable reliability (intraclass correlation coefficients 0.78–0.91) will be used. Firstly, participants will perform the heel-raise test, [41] which is recommended for the evaluation of calf muscle endurance in patients with AT. [42] Participants are asked to stand on one leg with a straight knee, supporting with their fingertips to the wall for balance. They are asked to perform as many heel raises as possible, with a straight knee and a frequency of one heel raise every 2 s, avoiding forward body sway. The test is terminated when the participant stops, cannot keep the frequency, or when the technique is incorrect for two consecutive repetitions. The total number of heel raises will be used for data analysis. Secondly, the one-legged countermovement jump (CMJ) will be used to evaluate jump height. [42] This test has previously been used as a functional outcome measure in patients with midportion AT. [25] Although jump height is determined by many other muscle groups, research has shown that the calf muscle complex accounts for an important part of the CMJ movement. [43].

The CMJ is performed with the participant in an upright position on a jumping platform (Projump, Biometrics, The Netherlands), with the hands placed behind the back. Participants are asked to quickly bend their knee as much as they want and then immediately jump upwards to their maximum height. They are allowed three maximal trials, and the best jump height (in cm) is used for data analysis. Pain during the heel raise tests and CMJ is recorded on a 0–10 numerical pain rating scale.

Differences in cost-effectiveness between both programs will be investigated by collecting several variables that are related to direct and indirect (medical) costs during follow-up assessments. These costs include medical consumption (visits to healthcare providers, supplementary diagnostics such as imaging, additional therapies such as insoles, braces, and medication use), and injury related absenteeism from (un)paid work, school, and sport.

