During the intervention period, participants are asked to refrain from other treatments and from anti-inflammatory medication related to their injury. If they receive other (medical) treatments after the intervention period, they are asked to register this in a logbook.

Participants in both study arms are advised not to participate in any tendon loading sports activities (i.e. walking, running and jumping) during the first 3 weeks of the intervention period. [23] Subsequently, they are allowed to resume tendon loading sports activities, as long as pain does not exceed 50 mm on a 0–100 mm visual analogue scale (VAS), and pain subsides within 24 h after the activity. [26].

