### Statistical analyses

Differences between the Alfredson and Silbernagel group will be analyzed according to intention-to-treat (ITT) principle. If necessary, missing data will be imputed using multiple imputation. Descriptive statistics will be calculated for all continuous variables, and means and SDs will be reported (or median and interquartile range for non-parametric data). For nominal and categorical data, proportions will be calculated and reported.

Baseline comparability of the two groups will be assessed by the Student t-test (parametric data), and non-parametric tests where appropriate. To assess differences in (pseudo)metric data within and between the groups over time, an analysis of variance (ANOVA) will be performed, with post-hoc tests to correct for multiple testing. Multivariate regression techniques will be conducted to model the prognostic value of baseline variables on outcome. The cost-effectiveness will be estimated by calculating the incremental cost-effectiveness ratio: (costs of Silbernagel program – costs of Alfredson program) / (health benefit of Silbernagel program – health benefit of Alfredson program), and will be expressed as costs per quality adjusted life year (QALY).

All analyses will be performed with statistical significance level set at α = .05 (two-sided).

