## Discussion

Several studies showed that both Alfredson isolated eccentric and Silbernagel combined concentric-eccentric training are beneficial in terms of symptom reduction in midportion AT. [14, 16, 17, 25, 26] However, whether any of these programs is more effective has yet to be determined. This study protocol describes the first RCT directly comparing the effectiveness of both programs. We designed a pragmatic study, in which we try to replicate how both programs are described in the clinical setting. By using the VISA-A – a condition-specific validated questionnaire that is widely recommended for use in research and clinical practice – as the primary outcome measure, we hope that comparison of our results to other studies and clinical practice will be enabled.

Besides the effectiveness on symptom reduction and QOL, our study also compares the effectiveness of both programs on functional performance of the muscle-tendon unit. This comparison has not previously been performed, whilst research has shown that functional deficits of the muscle-tendon unit may still persist after 1 year in patients with AT, even though symptoms have fully recovered. [45].

We will also assess differences in cost-effectiveness in the mid-term and long term. Cost-effectiveness may be an important parameter for clinical decision making, but to date, research investigating cost-effectiveness in AT treatment is scarce. [17] We expect no difference in direct intervention-related costs, since both programs are performed at home and the amount of supervising physiotherapy sessions is similar, but we are predominantly interested in potential differences in indirect costs (e.g. absenteeism of work, school and sports) between both programs.

Recruitment for this trial will be performed in different institutions, i.e. sports medicine clinics, hospitals, and general practices. Therefore, participant characteristics may differ, and this potentially could lead to different subgroups of participants. No stratified randomization for referral type is performed, but by including recreational athletes, it is expected that both study arms will consist of relatively homogeneous groups. Furthermore, we try to collect important participant characteristics that may cause potential bias to the results of this study. Nonetheless, it should be acknowledged that the participants’ metabolic health is not fully covered, whilst research showed that this may be a confounding factor. [46].

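### Missed recreational sport is classed as an indirect cost in a cost-per-QALY analysis; it belongs with the outcomes, outside the base-case cost numerator

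*Protocol article*

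**What the plan says.** The cost paragraph under Secondary outcome measures describes "collecting several variables that are related to direct and indirect (medical) costs during follow-up assessments". Its list of costs has two parts: medical consumption and "injury related absenteeism from (un)paid work, school, and sport". Table 2 places absence from sports activities in the block of cost-effectiveness variables, recorded at baseline and at 12, 26 and 52 weeks.

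The Discussion repeats the classification and gives it weight. It states "We expect no difference in direct intervention-related costs" and then "we are predominantly interested in potential differences in indirect costs (e.g. absenteeism of work, school and sports) between both programs".

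Statistical analyses defines the incremental ratio as the cost difference (Silbernagel minus Alfredson) over the difference in health benefit, which "will be expressed as costs per quality adjusted life year (QALY"). Quality of life is measured with the SF-12 and the EQ-5D; the article does not say which of them supplies the utilities.

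Two other sections bear on the point. Under Primary outcome measure, sporting function is one of the domains of the VISA-A. Under Intervention, both arms are "advised not to participate in any tendon loading sports activities" for the first three weeks, after which resumption depends on a pain threshold.

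**The concern.** A cost-per-QALY ratio keeps resources and lost production in the numerator and health effects in the denominator. Absence from work fits the numerator because output is lost. Missing a recreational run or match consumes nothing and loses no output. It is a consequence of symptoms, felt as lost function and enjoyment.

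Two things are at stake if the item is priced. First, the ratio depends on whatever value is put on a missed day or session of leisure sport, and such a value is hard to justify. Second, the program with less pain could be credited twice: once through better quality of life, and again through a lower cost that reflects the same improvement. Every participant takes part in tendon-loading sport by the inclusion criteria, so every participant can accrue the item.

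**Working it through.** **Step 1: is this a stated classification or an omission?** Three places agree. The cost paragraph lists sport absence as a cost, the Discussion calls it an indirect cost, and Table 2 groups it with the cost-effectiveness variables. It is therefore a stated choice, not a detail left to a fuller document.

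**Step 2: is it a cost or a health effect within this protocol?** The article treats sport limitation as health elsewhere: the VISA-A includes sporting function, and one pain scale concerns pain during sport. After week 3 sport is allowed only while pain stays within a limit, so from then on absence largely follows symptoms.

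**Step 3: how the item acts on the ratio.** The article gives no cost, unit value, utility or ratio, so there is no figure to reproduce. In symbols, let v be the money value of one day of sport absence, D the mean absence days per arm, ΔC the difference in all other costs, and ΔQ the QALY difference, each as Silbernagel minus Alfredson:

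ratio(v) = [ΔC + v × (D_S − D_A)] / ΔQ

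If v = 0, or if absence is equal in the two arms, the item has no effect.

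**Step 4: the three-week advice.** It is given to both arms. If all 21 days are counted in each, the contribution to the incremental cost is v × (21 − 21) = 0 for any v. Only absence that differs between arms can matter, mainly symptom-driven absence after week 3.

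**Step 5: illustration.** All inputs are assumptions: ΔC = 200 money units, ΔQ = 0.02, and fewer absence days in the Silbernagel arm. The choice of arm is arbitrary.

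| Value per day, v | 5 fewer days | 10 fewer days | 20 fewer days |
|---|---|---|---|
| 0 | 10,000 | 10,000 | 10,000 |
| 10 | 7,500 | 5,000 | 0 |
| 25 | 3,750 | -2,500 | -15,000 |
| 50 | -2,500 | -15,000 | -40,000 |

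For example, with 10 fewer days and v = 25: (200 − 25 × 10) / 0.02 = −50 / 0.02 = −2,500. With 10 fewer days the sign changes at v = 200 / 10 = 20 per day. The table shows that a chosen price can set both the size and the sign of the ratio. It does not estimate what will happen in this trial.

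**The case against.** The strongest reply is that double counting is not shown. It needs a positive money value on sport absence and a utility instrument that registers lost sport. The article states neither, and it does not describe the content of the SF-12 or EQ-5D. The cost paragraph speaks only of variables related to costs; if absence is merely counted in days, nothing enters the numerator. Valuation, perspective and utility source are also matters that a journal article may leave to the full plan. This stands as far as it goes: double counting is conditional, not a fact. It does not rescue the classification. If the item is priced, the ratio rests on an arbitrary value; if it is not priced, the text should not call it a cost.

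Two stronger readings are tempting and should not be drawn.

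- A reader might infer that the advised three weeks without tendon-loading sport distort the ratio. The advice is the same in both arms and cancels in the incremental cost under equal adherence.
- A reader might infer from the Discussion that sport absence will drive the numerator. The Discussion rules out only a difference in direct intervention-related costs. Care visits, imaging, aids, medication, and absence from work and school may all differ, and none of these can be sized from the article.

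It can also be said that absence from unpaid work and school follows from the same symptoms, and that whether lost leisure counts as a cost depends on a perspective the article does not state. That is a fair reason to allow a priced version as a sensitivity analysis. It is not a reason to put lost leisure in the base case.

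**Conclusion.** The point holds in a limited form. The article classes missed recreational sport as an indirect cost in a cost-per-QALY analysis, although it uses no resource, loses no production and, after week 3, follows pain. If it is priced, the ratio depends on an arbitrary value. If, in addition, the utility instrument captures lost sport, the same effect counts in both numerator and denominator. The size cannot be derived from the document; the figures in the working rest on assumed inputs throughout.

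This concerns a secondary economic evaluation alongside the trial. The primary VISA-A comparison is unaffected, and so is the sample size, which rests on VISA-A change scores only. It is a worthwhile and inexpensive correction, not a threat to the trial's main conclusion.

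**What to change.** In the cost paragraph of Secondary outcome measures, in Statistical analyses and in the Discussion, state that absence from sport is left out of the base-case cost numerator. Keep collecting it at the visits in Table 2 and report it by arm as a separate return-to-sport outcome. If a priced version is wanted, give the unit value with its justification and show the resulting ratio only as a labelled sensitivity analysis beside the base case.

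The cost is small: wording in three places, one item moved from costs to outcomes, and at most one extra analysis. No new data are needed.

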#### Other outcome measures

Morning stiffness is common in patients with AT, and is considered a good indicator of tendon recovery. [3] Participants will rate their morning stiffness (in minutes) in a logbook. This logbook is also used to record compliance to the exercise program. Compliance will be calculated by dividing the amount of exercises actually performed by the prescribed amount of exercises (i.e., 2× per day for the Alfredson group and 1×/day for the Silbernagel group). Subsequently, compliance will be categorized into four categories: poor (< 25%), moderate (between 25 and 50%), good (between 50 and 75%) and excellent (> 75%). [28].

Furthermore, participants will record other (medical) treatments and medication use in the logbook.

At baseline and follow-up measurements, the isometric strength of the hip extensors, abductors, and external rotators will be measured using a handheld dynamometer, according to previously reported methods. [44] Male patients with AT demonstrate diminished strength of their hip musculature compared to asymptomatic controls, [44] and by evaluating hip muscle strength over the course of this study, we try to investigate whether this is a prognostic factor in patients with AT.

### Measurements

All measurements will be conducted at baseline (T0), at 12 weeks (i.e. termination of intervention, T1), 26 weeks (T2), and at 52 weeks (T3) follow up, and include both the afore mentioned questionnaires and physical examination. Participants can complete the questionnaires online (secured environment), by using a hyperlink that will be sent to them by e-mail. All physical assessments are conducted by the same investigator (BH), who is blinded to group allocation. For a detailed overview of all outcome measures collected in the course of the study and the respective follow-up times, see Table 2.

**Table 2 Tab2:** Overview of outcome measures collected in the course of the study

	*Baseline*	*12 weeks*	*26 weeks*	*52 weeks*
Eligibility criteria check	*X*			
Body height	*X*			
Body weight	*X*	*X*	*X*	*X*
BMI	*X*			
Job type & activity level	*X*			
Sport type & activity level	*X*	*X*	*X*	*X*
Referral type	*X*			
Waist circumference	*X*			
Dorsiflexion ROM ankle	*X*			
Dorsiflexion ROM first MTPJ	*X*			
VISA-A score	*X*	*X*	*X*	*X*
VAS for pain during sport and daily activities	*X*	*X*	*X*	*X*
Morning stiffness	*X*	*X*	*X*	*X*
Global perceived effect (7-point scale)	*X*	*X*	*X*	*X*
Quality of life (SF-12 and EQ-5D)	*X*	*X*	*X*	*X*
Functional performance (CMJ and heel raise test)	*X*	*X*		*X*
Variables related to cost-effectiveness: - Medical consumption - Absenteeism from (un)paid work - Absenteeism from school - Absenteeism from sports activities	*X*	*X*	*X*	*X*
Compliance to exercise program		*X*		
Isometric strength of hip musculature	*X*	*X*		*X*

*BMI* body mass index, *ROM* range of motion, *MTPJ* metatarsophalangeal joint, *VISA-A* Victorian Institute of Sports Assessment – Achilles, *VAS* visual analog scale, *SF 12* 12-item short from health survey, *EQ-5D* Euroqol instrument, *CMJ* countermovement jump

### Statistical analyses

Differences between the Alfredson and Silbernagel group will be analyzed according to intention-to-treat (ITT) principle. If necessary, missing data will be imputed using multiple imputation. Descriptive statistics will be calculated for all continuous variables, and means and SDs will be reported (or median and interquartile range for non-parametric data). For nominal and categorical data, proportions will be calculated and reported.

Baseline comparability of the two groups will be assessed by the Student t-test (parametric data), and non-parametric tests where appropriate. To assess differences in (pseudo)metric data within and between the groups over time, an analysis of variance (ANOVA) will be performed, with post-hoc tests to correct for multiple testing. Multivariate regression techniques will be conducted to model the prognostic value of baseline variables on outcome. The cost-effectiveness will be estimated by calculating the incremental cost-effectiveness ratio: (costs of Silbernagel program – costs of Alfredson program) / (health benefit of Silbernagel program – health benefit of Alfredson program), and will be expressed as costs per quality adjusted life year (QALY).

All analyses will be performed with statistical significance level set at α = .05 (two-sided).

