### Sample size calculation

Sample size was calculated based on two high quality RCTs having investigated the Alfredson program and the Silbernagel program respectively, and using the VISA-A questionnaire as their primary outcome measure. [16, 26] We used the respective change (mean ± standard deviation [SD]) in VISA-A scores for the groups that followed the above-mentioned exercise programs:Rompe et al. [16] (*n* = 25): VISA-A Δ 22.4 ± 19 for the Alfredson programSilbernagel et al. [26] (*n* = 19): VISA-A Δ 34 ± 17 for the Silbernagel program

This resulted in an expected effect size of 0.64 between both exercise programs, with an expected VISA-A change score that exceeds the minimal clinically important difference of 10 points. [23] Using G*Power 3.1, and assuming α two-sided = 0.05 and a power of 0.80, a total of 39 participants in each study arm was required. The dropout rate in the above-mentioned studies was 4% [26] and 9% [16] respectively. We chose to take the most conservative dropout rate of 9% into account, resulting in a required amount of 86 in total, i.e. 43 participants in each arm.

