#### Primary outcome measure

The primary outcome for this study will be the difference in VISA-A scores between both programs after 12 months. The VISA-A questionnaire has been shown reliable and valid for evaluating clinical severity of symptoms of AT, [35] and was recently translated/validated in Dutch. [36] It consists of eight questions, covering the three domains of pain, and function in daily living and sporting activities. Scores range from 0 to 100, where 100 represents a perfect function.

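### The only stated between-group analysis, an ANOVA over time with corrected post-hoc tests, is not tied to the 12-month VISA-A contrast and does not secure the planned 80% power

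*Protocol article*

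**What the plan says.** Three parts of the protocol article bear on this point.

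- **Primary outcome measure:** "The primary outcome for this study will be the difference in VISA-A scores between both programs after 12 months". This is one contrast at one time. The Study objectives section sets the same 12-month horizon.
- **Sample size calculation:** the expected VISA-A changes are 22.4 (SD 19) for the Alfredson arm and "VISA-A Δ 34 ± 17 for the Silbernagel program", giving an effect size of 0.64. Then, "assuming α two-sided = 0.05 and a power of 0.80, a total of 39 participants in each study arm was required". With 9% dropout this becomes 43 per arm, 86 in total. No allowance for multiple comparisons is mentioned.
- **Statistical analyses:** for metric outcomes, the comparison of the arms is described thus: "over time, an analysis of variance (ANOVA) will be performed, with post-hoc tests to correct for multiple testing". One sentence covers every metric outcome. The section names no primary analysis and no time point, and does not say which or how many comparisons are corrected. It closes by setting a two-sided 0.05 level for all analyses.

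VISA-A is measured at baseline and at weeks 12, 26 and 52 (Measurements, Table 2).

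**The concern.** The trial is sized for one test and analysed with a method that yields several. A repeated-measures ANOVA of two arms gives a group main effect, a group-by-time interaction and a set of post-hoc contrasts. Only a between-arm contrast at week 52 answers the declared question.

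- If baseline is one of the levels, the main effect averages in a time point at which randomisation makes the expected difference zero.
- The interaction asks whether the two profiles differ in any way.
- The week-52 contrast appears at best among the post-hoc tests, which the text says serve to correct for multiplicity.

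At stake are the chance of detecting a true 12-month difference of the planned size and the meaning of a positive result. The candidate tests can disagree, and the stated analysis does not indicate which one decides the trial.

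**Working it through.** **Inputs from the Sample size calculation:** changes 22.4 (SD 19) and 34 (SD 17); two-sided 0.05; power 0.80; 39 evaluable per arm; 9% dropout. **Assumptions not in the article:** Bonferroni as the correction, the number of comparisons m, four occasions in the ANOVA, compound symmetry, and correlations r of 0.3 to 0.7 where they matter.

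**1. The plan's own figure.** Difference = 34 − 22.4 = 11.6. SD = √((19² + 17²)/2) = √325 = 18.03. Effect size d = 11.6/18.03 = 0.643. Noncentral t with 39 per arm (76 df, noncentrality 0.643 × √(39/2) = 2.84) gives 80.1% power at two-sided 0.05. Then 39/0.91 = 42.9, so 43 per arm and 86 in total. The plan's figure reproduces, for a single uncorrected comparison of change.

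**2. The same contrast as one of m corrected tests**, level 0.05/m:

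| m | level | power, 39 per arm | power, 43 per arm |
|---|---|---|---|
| 1 | 0.0500 | 80.1% | 83.9% |
| 2 | 0.0250 | 71.0% | 75.7% |
| 3 | 0.0167 | 65.3% | 70.5% |
| 4 | 0.0125 | 61.2% | 66.7% |

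Restoring 80% at m = 3 needs 53 per arm. 53/0.91 = 58.2, so 59 per arm and 118 in total.

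**3. The omnibus interaction.** With 39 per arm the test has 3 and 3 × 76 = 228 df. Its noncentrality is λ = (39/2) × Σ(xₜ − x̄)²/(σ²(1 − r)), where xₜ is the between-arm difference at each occasion. Reading 18.03 as the SD of change gives σ²(1 − r) = 18.03²/2 = 162.5, so the result does not depend on r. In units of 11.6:

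| Difference at weeks 0, 12, 26, 52 | Sum of squares | λ | Power |
|---|---|---|---|
| 0, 1, 1, 1 (constant) | 0.750 | 12.11 | 83.7% |
| 0, 0, 0, 1 (late) | 0.750 | 12.11 | 83.7% |
| 0, 1/3, 2/3, 1 (linear by visit) | 0.556 | 8.97 | 70.1% |
| 0, 1, 1/2, 0 (converging) | 0.688 | 11.10 | 80.0% |

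In the last row there is no 12-month difference, yet the test rejects 80% of the time.

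**4. The group main effect, if baseline is a level.** The noncentrality is (39/2) × x̄²/(σ²(1 + 3r)/4), with σ = 18.03/√(2(1 − r)). For r = 0.3, 0.5, 0.7, power is 95%, 76%, 46% for a constant effect; 67%, 43%, 23% for a linear one; and 23%, 14%, 9% for a late one.

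**5. The alternative.** A week-52 ANCOVA on baseline has residual SD σ√(1 − r²) = 14.5, 15.6, 16.6 for r = 0.3, 0.5, 0.7. Power at two-sided 0.05 with 39 per arm (75 df) is 93.6%, 90.0% and 86.0%.

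**The case against.** The strongest reply is that this is a condensed journal article. Model terms, the contrast that carries the primary test, and the correction family are usual content of a full protocol or analysis plan, and neither is shown. The primary question is fixed elsewhere in the article. A between-arm contrast at week 52 fits within the words about differences between groups over time, and the section's general 0.05 level would leave it at 80.1% power if it were tested alone.

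Much of this stands. A reader might infer that the stated analysis does not test the 12-month difference at all. The article does not support that, because the post-hoc tests may include it. A reader might also infer that power is certainly below 80%. That is not supported either:

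- No correction method or number of comparisons is given, and the correction might be meant for within-group or secondary comparisons.
- The interaction test has about 84% power for a constant or late effect.
- For raw week-52 scores at r = 0.3, power at 0.05/3 is still about 82% (65% at r = 0.5, 41% at r = 0.7).
- The inclusion of all four occasions is itself inferred from the phrase about change over time.

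What does not stand is that the matter is only missing detail. The article does state a method and a correction, and these do not match the basis on which it computes its sample size. The general 0.05 level does not resolve this, because the same section prescribes the correction.

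**Conclusion.** The point holds as a mismatch between three stated elements: a single 12-month contrast, a sample size for one uncorrected comparison, and an ANOVA over time with multiplicity-corrected post-hoc tests that neither isolates that contrast nor exempts it. The 80% is thus not secured by the analysis as written.

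The size of the loss is conditional. It is roughly 9 to 19 percentage points for the change-score contrast under Bonferroni with two to four comparisons, and nil if week 52 is tested alone at 0.05. The finding least dependent on unstated choices is that a significant group-by-time test would not establish a 12-month difference. That needs only the four occasions and compound symmetry for its figure, and no assumption about the correction.

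**What to change.** Name the between-arm VISA-A difference at 52 weeks as the single primary test, at two-sided 0.05 and without multiplicity correction. Take it from an ANCOVA at week 52 adjusted for baseline VISA-A, or from a linear mixed model on the three follow-up visits with arm, visit, arm-by-visit and baseline VISA-A. Report the 12- and 26-week differences as secondary estimates with 95% confidence intervals, and confine any correction to other time points and outcomes. If a correction is kept on the primary contrast, restate the power for the method and number of comparisons actually used, or resize the trial.

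The recommended change costs wording in the analysis section and the analysis plan. It needs no new data and no extra participants. The Trial status section reports 14 participants included by July 2017, so at that stage it could be settled well before any outcome analysis.

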## Methods/Design

### Study design and setting

This protocol was developed in accordance with the SPIRIT guidelines, [30] and describes an assessor blinded multicenter parallel-group RCT, with a one-year follow-up. The study will be conducted in two different centers, i.e. the University Medical Center Utrecht (UMCU, department of Rehabilitation, Physical Therapy Science & Sports), Utrecht, The Netherlands, and Papendal Sports Medical Center, Arnhem, The Netherlands. Participants will be randomized to a group performing either the Alfredson isolated eccentric or the Silbernagel combined concentric-eccentric exercise program. Randomization will be performed using a web-based randomization system, and allocation will be concealed. The investigators who are involved in baseline and follow-up measurements, and data analysis will be blinded to group allocation.

Measurements will be performed at baseline, and after 12, 26, and 52 weeks follow-up (see Fig. 1). The study protocol is in accordance with Declaration of Helsinki, and has been approved by the ethics committee of the UMCU (registration number 16–158). The protocol was registered with the Dutch Trial Register on 7 January 2016 (NTR5638). Written informed consent will be obtained from all participants prior to their participation.

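### The QALY difference in the cost-effectiveness ratio is given no adjustment for baseline EQ-5D; a regression on program and baseline utility would estimate it more precisely at almost no cost

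*Protocol article*

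**What the plan says.** Under Statistical analyses, the protocol article defines an incremental cost-effectiveness ratio. The numerator is the difference in costs between the programs. The denominator is given as "health benefit of Silbernagel program – health benefit of Alfredson program), and will be expressed as costs per quality adjusted life year (QALY").

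Under Secondary outcome measures, quality of life is assessed with the SF-12 and "the Euroqol instrument (EQ-5D) [40] during baseline and follow-up measurements". Under Measurements, the schedule is fixed: "All measurements will be conducted at baseline (T0), at 12 weeks (i.e. termination of intervention, T1), 26 weeks (T2), and at 52 weeks (T3) follow" … Table 2 marks quality of life at all four visits. The design is an "assessor blinded multicenter parallel-group RCT, with a one-year follow-up", so a one-year QALY can be built from these data.

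Baseline values have two uses in Statistical analyses. One is a check of the randomisation: "Baseline comparability of the two groups will be assessed by the Student t-test (parametric data"). The other is a regression on the prognostic value of baseline variables, which serves a separate aim. For differences within and between groups over time, "an analysis of variance (ANOVA) will be performed, with post-hoc tests to correct for multiple testing". No covariate is named for any between-program comparison.

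The Discussion acknowledges that recruitment from different institutions may produce subgroups, and adds: "No stratified randomization for referral type is performed, but by including recreational athletes, it is expected that both study arms will consist of relatively homogeneous" …

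**The concern.** A one-year QALY differs from most outcomes because the pre-randomisation measurement can be part of it. If the QALY is the area under the utility curve from week 0 to week 52, the first segment starts at the baseline value, which no exercise program has yet influenced. People who start with better utility also tend to have better utility later, so baseline enters a second time through correlation with the follow-up visits.

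With 43 participants per arm, some baseline difference in utility will arise by chance. In an unadjusted comparison part of that difference appears as health benefit of one program. The measurement needed to remove it is already scheduled. At stake is the precision of the denominator of the ratio, and how the QALY difference should be read once the baseline utilities are known.

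**Working it through.** **The plan's own figure.** The article gives no figure for EQ-5D or QALYs. Its only calculation is for VISA-A, and it supplies the arm size used below. Changes of 34 (SD 17) and 22.4 (SD 19) give d = (34 − 22.4)/√((19² + 17²)/2) = 11.6/18.03 = 0.643. A two-sided 0.05 t-test then needs 39 per arm (power 0.801), which agrees with "assuming α two-sided = 0.05 and a power of 0.80, a total of 39 participants in each study arm was required". Allowing 9% dropout, 39/0.91 = 42.9, so 43 per arm and 86 in total. The figure reproduces.

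**Inputs from the article.** Visits at 0, 12, 26 and 52 weeks; 43 per arm.

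**Assumptions, because the article does not give these.** QALY as the trapezoid area under the EQ-5D utilities; equal SD at each visit, 0.10 to 0.25; the same correlation ρ between any two visits, 0.3 to 0.7; no missing data.

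**Weights of the four visits in a 52-week QALY.**
- Week 0: (12/2)/52 = 6/52 = 0.115
- Week 12: (12/2 + 14/2)/52 = 13/52 = 0.250
- Week 26: (14/2 + 26/2)/52 = 20/52 = 0.385
- Week 52: (26/2)/52 = 13/52 = 0.250

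**Share of a baseline difference that carries into the QALY difference.** Slope = 0.1154 + 0.8846ρ.

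**Variance of the QALY, in units of the utility variance.** The squared weights sum to 0.286, so variance = ρ + (1 − ρ) × 0.286.

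**Share of that variance removed by adjustment.** Slope²/variance.

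| ρ | Slope | QALY variance | Variance removed |
|---|---|---|---|
| 0.3 | 0.381 | 0.500 | 29% |
| 0.5 | 0.558 | 0.643 | 48% |
| 0.7 | 0.735 | 0.786 | 69% |

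If the follow-up visits correlate at 0.5 with each other but only at 0.3 with baseline, the slope stays at 0.381, the variance becomes 0.602, and the share removed is 0.145/0.602 = 24%. This is the lower end of the range quoted.

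**Size of a chance imbalance.** The standard error of the baseline difference is SD × √(2/43) = 0.2157 × SD, which is 0.022 at SD 0.10, 0.043 at SD 0.20 and 0.054 at SD 0.25.

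**Shift in the QALY difference for an imbalance of one standard error.**
- Direct weight only: 0.115 × 0.022 = 0.0025 to 0.115 × 0.054 = 0.0062
- Full slope, smallest case (SD 0.10, ρ 0.3): 0.381 × 0.0216 = 0.008
- Full slope, middle case (SD 0.20, ρ 0.5): 0.558 × 0.0431 = 0.024
- Full slope, largest case (SD 0.25, ρ 0.7): 0.735 × 0.0539 = 0.040

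**If health benefit means gain over baseline instead.** Subtracting one year at the baseline utility changes the slope to 0.381 − 1 = −0.62, 0.558 − 1 = −0.44 and 0.735 − 1 = −0.27. The variance becomes QALY variance + 1 − 2 × slope from the table: 0.739, 0.528 and 0.317. Regression on baseline removes 0.62²/0.739 = 52%, 0.44²/0.528 = 37% and 0.27²/0.317 = 22% (computed with unrounded slopes). The regression estimate is therefore more precise under either reading.

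**The case against.** The strongest reply is that the article prints the textbook definition of the ratio and nothing more. A reader might infer that the plan commits to a raw difference of arm means. The text does not say that. The words raw and unadjusted do not appear, and a program coefficient from a regression is itself an estimate of the printed difference. The choice of utility instrument, the construction of the QALY and the covariates are often left to a fuller plan that is not shown. This stands, and it limits the point to an improvement of the stated formula rather than an error in it.

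A reader might also infer that the result would be biased. It would not be. Allocation is random, so the expected baseline difference is zero and the unadjusted difference is correct on average. What remains is avoidable variance and a shift conditional on the imbalance that occurs.

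Nor can it be said that the shift could reverse which program looks better, or how much power would be gained. The article gives no expected QALY difference, no EQ-5D standard deviation and no power for the economic analysis.

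Two further replies carry weight. The area-under-curve construction is an assumption, and under a gain-over-baseline definition the program that starts better would be penalised, not credited. And most of the carry-over is ordinary correlation with later visits: at ρ 0.5, 0.442 of the 0.558. The Discussion also says that the interest lies mainly in indirect costs, which belong to the numerator. None of this argues against adjusting, because the regression is the more precise estimate in both constructions.

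**Conclusion.** The point holds as a low-severity improvement to a secondary economic analysis. The plan states the QALY difference without baseline adjustment and provides none elsewhere, although the baseline utility is collected. If QALYs are the area under the four utilities and are compared unadjusted, about 0.38 to 0.73 of a chance baseline difference carries over. An imbalance of one standard error then moves the QALY difference by 0.008 to 0.040, and adjustment would cut the variance by roughly 24% to 69%.

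The weights follow from the visit schedule. Everything else rests on the assumed SD (0.10 to 0.25), the assumed correlations (0.3 to 0.7) and 43 complete participants per arm. The primary VISA-A comparison and the sample size are unaffected.

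**What to change.** Add to Statistical analyses, or to the analysis plan if one exists: the incremental QALY is the program coefficient from a linear regression of 52-week QALYs (area under the EQ-5D utilities at 0, 12, 26 and 52 weeks) on program and baseline EQ-5D utility; this estimate is the denominator of the cost-effectiveness ratio, and the unadjusted difference in arm means is reported beside it.

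The cost is one sentence and one regression on data already scheduled, with no new measurements or participants. The adjusted figure will no longer equal the simple difference of arm means, which is why both should be shown. The article's Trial status section reports 14 of the planned 86 participants included on 3 July 2017, so at that stage the choice could still be fixed well before analysis.
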